### Measures

*Primary outcome:* The primary outcome will be change in cIMT over 24 months from randomization.

*Secondary outcomes;* will include progression of CKD, death as a consequence of CKD/CVD, periodontal status, endothelial function, arterial stiffness, measures of inflammation and infection, CVD risk factors (blood pressure, total cholesterol, HDL-cholesterol, HbA1c), CV events (myocardial infarction, coronary revascularisation procedures, ischaemic cerebrovascular disease, peripheral vascular disease, ischaemic stroke) and oral health-related quality of life. Progression of CKD will include time to the development of the first of: (1) new development of macroalbuminuria (defined as ACR ≥30 mg/mmol); (2) 30 % loss of baseline eGFR (defined as a reduction of eGFR of 30 % or more from baseline and eGFR of less than 60mLs/min/1.73 m2); (3) progression to ESKD defined by eGFR <15 mLs/min; (4) progression to ESKD defined by commencement of renal replacement therapy.

### Data collection techniques

Both clinical and self-report information will be gathered in this study.

*Clinical*: Each participant will receive CKD/CVD, cardio-metabolic-related and dental assessments at four time points throughout the study (baseline, 6 months, 12 months and 24 months post randomization).

#### CKD/CVD and cardio-metabolic-related assessments

Markers of renal function will be assessed by ACR and eGFR. eGFR will be assessed using the CKD-EPI formula: eGFR = 141 × min(Scr × 0.0113/k, 1)^α^ × max(Scr × 0.0113/k, 1)^−1.209^ × 0.993^Age^ × 1.018 [if female], where Scr is serum creatinine concentration in μmol/L, k is 0.7 for females and 0.9 for males, α is −0.329 for females and −0.411 for males, min indicates the minimum of Scr/k or 1 and max indicates the maximum of Scr/k or 1. Maple-Brown and colleagues demonstrated that the correction factor “if black” is not applicable to Aboriginal Australians [47].

Markers of systemic inflammation will be assessed by CRP, serum amyloid A, fibrinogen, neutrophils and total IgG. Standard Framingham risk factors will be assessed (non-fasting lipids, blood pressure, diabetes control (HbA1c), BMI and tobacco smoking) as well as waist-hip ratio and medications including ACE inhibitors and angiotensin receptor blockers. Peripheral blood pressure will be measured and central pressure calculated (SphygmoCor XCEL).

Markers of cardiovascular health will be measured by: (1) cIMT; (2) endothelial function; (3) arterial stiffness and; (4) additional CVD risk factors.Common carotid intima-media thickness (IMT)External ultrasound of the common carotid artery will be performed with the patient lying in a supine position, neck slightly extended and the head tilted 45° away from the side being scanned whilst connected to 3-lead ECG, to monitor cardiac cycle. Bilateral longitudinal images of the carotid bulb and common carotid artery, up to 10 mm proximal to the bulb, will be obtained using a portable ultrasound (Sonosite, Bothell, USA) with a 10–5 MHz linear array transducer. Both the right and left carotid arteries will each be scanned from three angles, with two loops obtained from each scan angle, and stored in a digital format for batch analysis by an observer blinded to participant characteristics, randomization and study visit. Measurement of carotid IMT will be performed on the far wall of the common carotid artery at end diastole, within 10 mm proximal to the carotid bulb, from at least two consecutive cardiac cycles.Endothelial function—brachial artery flow-mediated dilatation (FMD)High-resolution ultrasound will be used to assess brachial artery diameter at rest, and after a hyperaemic stimulus in response to a 5 min forearm occlusion. A 30 s loop will be acquired at rest, and three 30 s loops acquired post-hyperaemia from 30–60 s, 60–90 s, and 90–120 s. Response to sublingual nitroglycerin, a smooth muscle dilator, will not be determined to minimize participant burden.Arterial stiffness—carotid-femoral pulse wave velocityPulse wave velocity along the aortic transit will be assessed using a SphygmoCor XCEL device (Atcor medical). This validated device assesses carotid and femoral pulses concurrently by handheld tonometer and thigh cuff, respectively. Distance from the suprasternal notch to the two sites will be measured immediately after data capture. Two measures of pulse wave velocity will be made, with a 1 minute interval.History and incidence of cardiovascular and cerebrovascular events will be defined as coronary heart disease (myocardial infarction, angina pectoris, coronary revascularisation procedures), ischaemic cerebrovascular disease, peripheral vascular disease and transient ischaemic attack.

Dental assessment: This will include tooth presence, caries experience, periodontal destruction, gingivitis and calculus, plaque, oral mucosal lesions and trauma.

##### Self-report

Self-report information pertaining to socio-demographic, oral health and general health factors will be gathered at baseline.

Socio-demographic factors: These will include age, sex, education level, employment, English-as-first-language, house ownership, number of children and number of people who stayed in house the previous night.

Oral health factors: These will include self-reported oral health, oral health behaviours and oral health-related quality of life.

General health factors: These will include behaviours such as smoking and alcohol consumption, current medication, current diagnoses (for diabetes, cardiovascular disease, hypertension etc.), status of current diagnoses (controlled, uncontrolled etc.) and stress (measured by an adapted PHQ9 scale; a measure of distress that has been validated for Aboriginal adults; [48]).

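### Oral health-related quality of life is a secondary outcome, but baseline is the only collection time the text gives for it; the two sections need reconciling

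*Protocol article*

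**What the plan says.** All references are to the protocol article.

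- **Measures.** The list of secondary outcomes ends with "ischaemic stroke) and oral health-related quality of life".
- **Self-report.** The block opens with its timing: "Self-report information pertaining to socio-demographic, oral health and general health factors will be gathered at baseline". Within it, the oral health factors are "self-reported oral health, oral health behaviours and oral health-related quality of life". No later time is given for this block.
- **Data collection techniques (clinical).** A separate schedule applies to clinical data: "Each participant will receive CKD/CVD, cardio-metabolic-related and dental assessments at four time points throughout the study". The four times are baseline, 6, 12 and 24 months.
- **CKD/CVD and cardio-metabolic-related assessments, dental assessment.** The content of the repeated dental examination is: "This will include tooth presence, caries experience, periodontal destruction, gingivitis and calculus, plaque, oral mucosal lesions and trauma".
- **Follow up.** All participants come to the clinic at 6, 12 and 24 months.
- **Data analysis, Aim 2.** Each secondary outcome gets its own mixed model with treatment group as a fixed effect (a generalised mixed model if the outcome is not continuous). Effect sizes are to be built from change scores.

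**The concern.** An outcome in a randomised trial needs at least one value measured after randomisation. Here the outcome list promises a between-arm comparison of oral health-related quality of life, while the data collection text gives it one time point, and that is baseline. A site team working from this text would have no instruction to repeat the questionnaire.

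What is at stake is the whole of one declared secondary outcome. The loss would also be permanent. According to the abstract, the delayed group receives its treatment 24 months after baseline, so once that has begun no untreated comparison remains. An analysis plan cannot repair the gap afterwards, because it cannot analyse values that were never collected.

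**Working it through.** The protocol gives no sample size, power or effect figure for this outcome, so there is no stated number to reproduce. The check is a cross-reading, followed by what the planned model can estimate.

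**Step 1. Is it an outcome?** Yes. Measures names it among the secondary outcomes.

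**Step 2. Which schedule applies to it?** Data collection techniques divides the information into clinical and self-report.

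| Type of information | Stated times | Includes quality of life? |
|---|---|---|
| Kidney, cardiovascular and cardio-metabolic assessments | Baseline, 6, 12, 24 months | Not listed |
| Dental assessment | Baseline, 6, 12, 24 months | Not listed; the items are clinical findings |
| Self-report: socio-demographic, oral health and general health factors | Baseline | Yes, under oral health factors |

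**Step 3. Could it enter follow-up by another route?** The only plausible one is the repeated dental assessment, and its item list contains no questionnaire. No other section gives a later time for this outcome.

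**Step 4. Count the stated time points.** Follow up sets 3 post-randomisation visits. The number with a stated quality-of-life measurement is 0, so coverage as written is 0/3. Counting baseline as well, it is 1 of 4.

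**Step 5. What can the planned analysis estimate from that?** Write Y(i,t) for participant i at time t and G(i) for the arm.

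- A change score is Y(i,t) − Y(i,0) with t = 6, 12 or 24. With t = 0 alone, none exists.
- With only Y(i,0), the mixed model reduces to Y(i,0) = b0 + b1·G(i) + error. If the baseline questionnaire is completed before treatment and before the arm is known (an assumption; the article does not give the order of events at the baseline visit), randomisation makes the expected value of b1 zero. A test at the planned 0.05 level would then reject about 5% of the time, whatever the true effect of the intervention.

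The model would therefore measure chance imbalance between the arms at baseline and not a treatment effect.

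**The case against.** The strongest case against is that the text is loosely worded, and that no decision was made to measure once.

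- **No exclusive wording.** The Self-report section gives baseline as a time but does not say it is the only one. This stands.
- **The baseline sentence is not a strict schedule for everything beneath it.** Smoking and current medication are in the self-report block, yet tobacco smoking and medications also appear among the assessments repeated at four time points. Some self-report topics are therefore recorded again. This stands and weakens the literal reading, but quality of life has no second listing of that kind.
- **The study schema is not visible.** Fig. 1 might show when questionnaires are given. This stands as a limit on certainty.
- **Other text points towards follow-up.** Calling it an outcome, bringing everyone back three times and planning a model for each outcome all suggest that repetition was intended. That is plausible, but it restates the inconsistency without removing it.
- **An article may leave a questionnaire schedule to the full protocol.** It may. This article does give a time, however, and that time conflicts with its own outcome list, so this goes beyond an omitted detail.

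A reader might infer that the trial has deliberately fixed a single measurement, so that all endpoint data for this outcome are missing by design. The document does not support this, for the first three reasons above. A reader might also infer that a different analysis is needed, such as a baseline-adjusted comparison at 24 months alone. Nothing in the document calls for it: the mixed model already planned is adequate once follow-up values exist.

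**Conclusion.** The inconsistency holds. A declared secondary outcome has baseline as its only stated collection time, and following the text as written gives 0 of 3 follow-up measurements and no estimable treatment effect. This rests on two conditions: that the schema not shown does not schedule the questionnaire at later visits, and that sites follow the wording of the Self-report section literally. If either fails, the remaining problem is one of wording.

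The size is limited. One secondary outcome is affected, named last in its list and absent from the Aim 2 hypothesis and from the outcomes given in the abstract. The primary analysis of carotid intima-media thickness, the sample size and the randomisation do not depend on it. It would be going too far to say that the trial's main result is at risk, since no primary quantity uses this measure. The right grade is should-fix. It is worth acting on before follow-up visits pass, because a missed measurement cannot be recovered.

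**What to change.** Reconcile Measures and Self-report in one of two ways.

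1. **Keep the outcome.** Amend the Self-report section to say that the oral health-related quality-of-life questionnaire is given at baseline and at the 6-, 12- and 24-month visits. If burden is a concern, the minimum is baseline plus 24 months, with the 24-month questionnaire completed before any delayed treatment begins. Socio-demographic items can stay at baseline. Analyse it with the mixed model already set out under Data analysis, Aim 2. If the schema or full protocol already schedules these visits, one sentence in the text is enough.
2. **Drop the outcome.** If a single baseline measurement is truly intended, remove oral health-related quality of life from the secondary outcomes and describe it as a baseline characteristic.

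The first option costs a short questionnaire at visits that all participants already attend and for which they are already reimbursed, plus the added data entry. The article names no instrument, so the time per participant cannot be stated. The second option costs nothing in the field but gives up the comparison.

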### Reimbursement for time

As per our standard procedures for Aboriginal participants involved in periodontal interventions, all participants will receive a $AUS20 gift voucher at baseline, 3-, 6-, 12- and 24-month follow-up as reimbursement for time. Each participant will additionally receive free periodontal care and a sample bag of oral health-related items.

### Data analysis

Data analysis will use intention-to-treat and per-protocol approaches, with the effect on primary outcomes based on intention-to-treat analyses. Analyses will follow a general course of descriptive statistics such as distributions and measures of association. Simple cross-tabulations and more elaborate repeated-measures analyses will follow. In brief, the plan for the analysis of each aim is:*Aim 1: Extent and severity of periodontal disease compared with national-level counterparts:* Extent of periodontal disease will be defined by the number of periodontal sites in the mouth with a given pocket depth (PD) divided by the number of teeth in the mouth x 100. The National Survey of Adult Oral Health dataset will enable comparison with both general and Aboriginal population-level estimates [49]. General analysis will comprise Chi-square and Student’s t-test within the study sample and non-overlapping 95 % confidence intervals when comparing with population estimates.*Aim 2: Changes in cIMT, measures of renal function and CKD/CVD-related death:* The primary analysis will compare changes in cIMT and 95 % confidence intervals. Secondary analyses will examine each outcome variable using separate mixed models, to allow inclusion of all participants without having to impute data. We will use generalised linear mixed models for non-continuous outcomes. Models will include treatment group as a fixed effect. Analyses will be conducted to identify subgroups that modify the response to the intervention (eg. active/passive smoking, socio-economic status). Model assumptions will be checked and appropriate adjustments made. We will conduct sensitivity analyses to assess uncertainty in key parameters. Death and cardiovascular events, both binary outcomes, will be analysed using the chi-square test with frequencies and percentages per treatment arm and odds-ratios or other measures of treatment effect reported along with summary measures. The Greenhouse-Geisser correction for the F-test will be used to adjust the degrees of freedom for deviation from sphericity. Logarithmic transformation of the data will be performed where appropriate. A post hoc correlation analysis by the Spearman rank-correlation method will be performed to evaluate the relationship between the changes in renal function and cIMT from baseline to 6, 12 and 24 months following periodontal therapy. The same will also be done for measures of periodontal health and cIMT. Effect sizes will be calculated by dividing the mean of change scores by the pooled estimate of the standard deviation. Effect measures will also be presented through calculation of number-needed-to-treat and its associated 95 % confidence interval. The statistically significant level will be at α < 0.05.

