### Aims and hypotheses

The goals are to assess levels of periodontal disease among a group of Aboriginal adults with CKD and to determine if comprehensive periodontal therapy might reduce progression of CKD, non-invasive measures of cardiovascular disease (CVD) or CKD/CVD-related death amongst people with CKD over 6 to 24 months. The specific aims and hypotheses are:Aim 1: To describe the extent and severity of periodontal disease in a group of Aboriginal adults with CKD.*Hypothesis: The extent and severity of periodontal disease in an Aboriginal population with CKD will be high compared with national-level indicators.*Aim 2: To examine the effects of a comprehensive periodontal intervention among an Aboriginal population with CKD.*Hypothesis: Exposure to a comprehensive periodontal intervention will reduce progression of CKD, non-invasive measures of CVD or CKD/CVD-related death amongst those with CKD.*

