### Inclusion criteria

Aboriginal people aged 18+ years who have lived in the study location for 2+ years, and who plan to live at their current location for the next 2 years, with CKD (i. on dialysis; ii. eGFR levels of <60 mls/min/1.73 m^2^ (CKD Stages 3 to 5); iii. ACR ≥30 mg/mmol irrespective of eGFR (CKD Stages 1 and 2); iv. diabetes plus albuminuria (ACR ≥ 3 mg/mmol) irrespective of eGFR), with at least 12 teeth at baseline and having moderate or severe periodontal disease will be invited to take part in the study. Periodontal disease will be assessed using the US Centers for Disease Control and Prevention and the American Academy of Periodontology definitions, whereby a case of moderate periodontitis is considered as the presence of either two sites between adjacent teeth with 4 mm + attachment loss or at least two such sites with 5 mm + pockets, and severe periodontitis as having at least two sites between adjacent teeth with 6 mm + attachment loss and at least one 5 mm + pocket [44].

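### Extent of periodontal disease is defined as affected sites over teeth, giving a rate per 100 teeth whose scale depends on how many sites per tooth are probed

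*Protocol article*

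**What the plan says.** The Aim 1 hypothesis in Aims and hypotheses is comparative: "The extent and severity of periodontal disease in an Aboriginal population with CKD will be high compared with national-level indicators".

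The Data analysis section then gives the formula for extent: "number of periodontal sites in the mouth with a given pocket depth (PD) divided by the number of teeth in the mouth", times 100. On the comparator it says: "The National Survey of Adult Oral Health dataset will enable comparison with both general and Aboriginal population-level estimates". The decision rule is "non-overlapping 95 % confidence intervals when comparing with population estimates".

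Elsewhere the article treats sites and teeth as different units. Inclusion criteria sets a tooth count ("with at least 12 teeth at baseline and having moderate or severe periodontal disease"), while its definition of moderate periodontitis counts sites: "two sites between adjacent teeth with 4 mm + attachment loss or at least two such sites with 5 mm + pockets".

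The dental assessment is described only in general terms: "This will include tooth presence, caries experience, periodontal destruction, gingivitis and calculus, plaque, oral mucosal lesions and trauma". The number of sites probed per tooth is given neither for the trial nor for the national survey.

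**The concern.** A figure multiplied by 100 and called extent will be read as a percentage. As written it cannot be one, because a tooth can contribute several sites to the numerator but only one unit to the denominator. The value therefore rises with the number of sites probed per tooth, even when the share of diseased sites is unchanged.

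This matters because extent is one of the two quantities in the Aim 1 hypothesis and will be judged against outside population figures by whether confidence intervals overlap. A pure difference of scale can separate two intervals. If the trial's index were set against population estimates expressed as percent of sites, the distortion would run in the hypothesised direction, making the trial sample look worse.

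**Working it through.** The article reports no value for extent, so there is no figure of its own to reproduce. The check is on the formula.

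**Inputs**
- Formula: affected sites divided by teeth, times 100 (Data analysis, Aim 1).
- Minimum number of teeth: 12 (Inclusion criteria).
- Sites probed per tooth, *s*: not stated. Assumed range 1 to 6.
- Share of probed sites affected, *p*: illustrative.

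**Algebra.** With *T* teeth, *s*·*T* sites are examined and *p*·*s*·*T* are affected.
- Index as written: 100 × (*p*·*s*·*T*)/*T* = 100·*p*·*s*.
- Percent of sites: 100 × (*p*·*s*·*T*)/(*s*·*T*) = 100·*p*.

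The number of teeth drops out of both. The index as written is *s* times the percent of sites.

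**Ceiling and crossing point of the index as written**

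| *s* (assumed) | Maximum (100·*s*) | Share of sites at which it reaches 100 (1/*s*) | Value when 20% of sites are affected |
|---|---|---|---|
| 1 | 100 | 100% | 20 |
| 2 | 200 | 50% | 40 |
| 3 | 300 | 33.3% | 60 |
| 4 | 400 | 25% | 80 |
| 6 | 600 | 16.7% | 120 |

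With sites examined as the denominator, the last column would be 20 in every row and the maximum would be 100.

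**One participant.** Take 12 teeth with 20 affected sites. The index as written is 20/12 × 100 = 166.7. Under an assumed six-site scheme, 12 × 6 = 72 sites are examined, and the percent of sites is 20/72 × 100 = 27.8.

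**Effect on the comparison with the survey**
- *Same formula, different probing.* For the same share of sites affected, the two values stand in the ratio *s*(trial)/*s*(survey). If the trial used 6 and the survey 3, the ratio would be 6/3 = 2.0, for example 120 against 60 with 20% of sites affected in both. If the survey probed more sites than the trial, the distortion would run the other way.
- *Index against percent of sites.* The trial value is too large by the factor *s*.
- *Index against percent of teeth.* The factor is the mean number of affected sites per affected tooth, which lies between 1 and *s*.
- *Same formula, same probing.* Both values and both confidence intervals are multiplied by the same *s*. The ratio is unchanged, and so is whether the intervals overlap.

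**The case against.** The strongest reply is that the index is oddly scaled but usable. Read as affected sites per 100 teeth it is a legitimate rate, and the article never calls it a percentage. The article also refers to the national survey's dataset, so the same formula can be run in both sources. If the sites per tooth agree, nothing is lost. This stands, and it limits the point.

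A reader might infer that the definition invalidates the Aim 1 comparison. The documents do not support that. They do not show that the two probing schemes differ, nor that published percentages will be used as the comparator. Equally, they speak of population-level estimates and do not commit to recomputing the survey with this formula, so the risk is open rather than demonstrated. The two-fold example above is a hypothetical, not a property of this plan.

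A reader might also infer that periodontal status at follow-up will be misstated. Periodontal status is a secondary outcome, but nothing in the article says that this formula will be used for it. Randomised arms examined in the same way would share the same scale factor in any case.

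Two further replies have some force. Enrolment already requires moderate or severe periodontitis, so a high extent relative to the population is partly built in, and a new denominator is unlikely to reverse that direction. It would still change the reported size. And a condensed article may leave the pocket-depth threshold, the probing scheme and the harmonisation with the survey to a fuller document. Their absence is not the complaint here. The complaint is about a formula that the article does state and that mixes units on its face.

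**Conclusion.** The concern holds as a definition error that should be fixed. Extent as written equals 100 times the share of sites affected times the sites probed per tooth. It can exceed 100 whenever more than one site per tooth is probed, and under an assumed 2 to 6 sites its ceiling is 200 to 600. The unit mismatch follows from the text alone; every numerical size rests on the assumed number of sites per tooth.

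Whether the comparison is distorted depends on what the index is set against. The factor cancels when the survey is analysed with the same formula and sites per tooth, and does not otherwise.

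The reach is limited to the extent half of a descriptive aim. Severity, eligibility, the sample size, the primary cIMT outcome and the randomised treatment comparison do not use this formula.

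**What to change.** Redefine extent as the number of sites at or above the stated pocket-depth threshold, divided by the number of sites examined, times 100. If a tooth-level measure is wanted, use teeth with at least one such site divided by teeth examined, times 100.

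State the sites probed per tooth for the trial and for the national survey. Compute the survey values from its dataset with the same formula, restricted to the sites common to both. The restriction is needed because percent of sites also depends on which sites are probed, so changing the denominator alone does not make the two sources comparable.

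The cost is one sentence in the plan and about one line of code, provided the number of sites examined is recorded for each participant. The article does not describe the recording scheme, so that should be confirmed.

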### Periodontal disease and Aboriginal Australians

Although representative national-level data are unavailable, estimates from convenience samples indicate that periodontal disease is a substantial problem among Aboriginal Australians. The prevalence of periodontal disease among Aboriginal participants seeking care at the Redfern Aboriginal Medical Service was around 60 % [19], while the prevalence was approximately 90 % in a recent convenience sample in the Northern Territory [20].

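### Aim 1 plans inference against Aboriginal population estimates from a national survey, although the Background says representative national data are unavailable; the two statements must be reconciled and the Aim 1 claim narrowed

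*Protocol article*

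**What the plan says.** The Aim 1 hypothesis (protocol article, Aims and hypotheses) reads: "The extent and severity of periodontal disease in an Aboriginal population with CKD will be high compared with national-level indicators".

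The Data analysis section names one external source, the National Survey of Adult Oral Health, which "will enable comparison with both general and Aboriginal population-level estimates". The rule for those external contrasts is "non-overlapping 95 % confidence intervals when comparing with population estimates".

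The Background, under Periodontal disease and Aboriginal Australians, states: "Although representative national-level data are unavailable, estimates from convenience samples indicate that periodontal disease is a substantial problem among Aboriginal Australians".

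Under Inclusion criteria, Aboriginal adults with CKD "with at least 12 teeth at baseline and having moderate or severe periodontal disease will be invited to take part in the study".

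**The concern.** A national survey that gave valid estimates for the Aboriginal population would be the kind of source that the Background reports as lacking. If the survey's Aboriginal respondents are not representative, a confidence interval computed from them is not an interval for the Aboriginal population value. Comparing it with the trial's interval then supports no population statement in either direction.

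Followed as written, the plan could therefore produce a published inference that the protocol's own Background undercuts. The source, the comparator and the decision rule are all fixed in the article, so this is more than detail left to a later plan. What is at stake is the Aim 1 conclusion only. The randomised comparison, the cIMT primary outcome and the sample size do not depend on it.

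**Working it through.** The article gives no reference estimate, effect size or sample size for Aim 1, so there is no planned figure to reproduce. The check is one of consistency, with supporting arithmetic.

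**1. The two statements side by side.**
- Background: representative national-level data unavailable; only convenience-sample estimates are cited.
- Data analysis: a national survey supplies Aboriginal population-level estimates, to be compared by interval overlap.

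They can be reconciled in two ways. Either the survey's Aboriginal estimates are representative and the Background needs correcting, or they come from a subsample that is not representative and the inferential use must go. The document does not show which is true.

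**2. What remains if the Aboriginal comparator is not inferential.** The hypothesis refers to national-level indicators. The general-population estimates from the same survey fit that wording, so Aim 1 keeps a comparator.

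**3. How the overlap rule behaves.** Let r be the ratio of the two standard errors. With no true difference, two 95 % intervals fail to overlap with two-sided probability 2 × [1 − Φ(1.96 × (1 + r) / √(1 + r²))]. The value of r is assumed, because the document gives no standard errors. The formula is unchanged when r is replaced by 1/r, so 0 to 1 covers all cases.

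| r | 1.96 × (1 + r) / √(1 + r²) | Two-sided error |
|---|---|---|
| 1 | 2.77 | 0.0056 |
| 0.5 | 2.63 | 0.0085 |
| 0.25 | 2.38 | 0.017 |
| 0.1 | 2.14 | 0.032 |
| 0 | 1.96 | 0.050 |

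The rule is conservative, by an amount that depends on the survey's precision. It does not itself create a false finding of high disease, but its error rate is not fixed at the stated 0.05 and it yields no estimate of the difference. A difference with its own 95 % interval does both jobs.

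**4. Effect of eligibility on the general-population contrast.** Inputs: the planned 600 participants (Sample size) and the disease requirement (Inclusion criteria).
- Prevalence of moderate or severe disease among those enrolled is 600/600 = 100 % by design. The exact lower 95 % limit is 0.025^(1/600) = 0.994. On prevalence, the overlap rule would declare the sample high against any comparator whose interval lies below 99.4 %.
- For extent, suppose a fraction p of the comparator population are cases, non-cases contribute about zero, and cases are equally affected in both groups. Enrolling only cases then multiplies mean extent by 1/p: 1/0.20 = 5.0, 1/0.30 = 3.3, 1/0.50 = 2.0, 1/0.90 = 1.1. These values of p are assumed. If non-cases contribute more than zero, the factor is smaller.

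Standardising for age and sex does not remove this selection, so it must be stated with the result.

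**The case against.** The strongest reply is that this is a wording tension about one of two comparators in a descriptive aim. That is fair as to scale, and several stronger readings do not stand.

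- A reader might infer that Aboriginal estimates do not exist. The Background says only that representative national-level data are unavailable. The survey may hold a usable Aboriginal subsample, and the document cannot settle that.
- A reader might infer that Aim 1 cannot show high disease at all. That does not follow, because the hypothesis is framed against national-level indicators and the general-population contrast is still there. Nor does the protocol state an aim of separating a CKD-related excess from an excess in Aboriginal adults generally.
- A reader might infer that the general-population contrast is planned as a crude one. The section describes itself as brief and is silent on standardisation. Silence in an article is not an error, so standardisation is offered here as a better method than the overlap rule and not as the correction of a stated mistake.
- A reader might use the Background's convenience-sample prevalences, about 60 % and about 90 %, to argue that the conclusion depends on the comparator chosen. The plan names neither as a comparator, and a prevalence below 100 % cannot arise in a sample enrolled on having the disease.

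What the reply does not remove is the conflict itself. The plan attaches an inferential rule to Aboriginal population estimates that the Background gives reason to doubt, and a reader of the results could not tell which statement to rely on.

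**Conclusion.** The point holds in a limited form. The Background and the Data analysis section conflict on whether representative national data exist for Aboriginal Australians, and the plan draws inference on the side that the Background disowns. Unless representativeness is documented, no conclusion against the Aboriginal population is supported.

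The general-population contrast is legitimate for the hypothesis as worded, but it describes trial participants selected for disease and for having at least 12 teeth, and not Aboriginal adults with CKD as a whole. This assumes that Aim 1 uses enrolled participants. The within-sample tests in the Data analysis section point that way, and the article does not say that everyone screened will be analysed.

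The consequence cannot be put in Aim 1 units, because no reference figure is given. The error rates and the 1/p factors above are illustrations that rest on the assumptions stated with them. The matter is modest and confined to Aim 1.

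**What to change.** 1. Reconcile the two sections. If the survey's Aboriginal estimates are representative, document this and correct the Background.
2. Otherwise, remove the Aboriginal comparison from the inferential plan. Report the survey's Aboriginal respondents descriptively, with their number and confidence interval, and draw no conclusion against the Aboriginal population.
3. For the general population, replace the interval-overlap rule by an age- and sex-standardised difference with its 95 % confidence interval. Age and sex are already collected (Self-report), and the survey dataset is already named.
4. State with the Aim 1 result that it describes a sample selected for moderate or severe periodontal disease and at least 12 teeth, and not the Aboriginal CKD population.

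The cost is wording changes and one standardisation step. No new data are collected from participants. The downside is that Aim 1 makes a narrower claim.
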